### Primary outcome measures

Recruitment rate, including proportion of ineligible patients and reasons for non-consentInformation on the ideal method of randomisation, which will include calculation of intra-cluster correlation co-efficient to investigate whether there is any inherent clustering in outcomes based on which ward bay a participant is admitted toAdherence to protocol, and reasons for non-adherence, as defined by the number of patients who do not receive the correct type of monitoring as per randomisation (and reasons for this) and the number of patients who do not wear the patch for their entire hospital stay or at least 5 days during their admissionAmount of missing clinical data, as collected on the Case Report Forms, and loss-to-follow-upOptimal outcome measures to test effectiveness (see secondary outcome measures)Estimation of parameters to input into the sample size calculation for a definitive RCT.

### Secondary outcome measures

Time to antibiotics in cases of sepsisNumber of HDU/ICU admissionsLength of stay in HDU/ICUTotal length of stay in hospitalNumber of postoperative complications, defined and scored according to the Clavien-Dindo classification of surgical complications [10]Number of reinterventions, defined and scored according to the Clavien-Dindo classification of surgical complications [10]Patient acceptability using questionnaire scoresNumber of patients not wearing patch for at least 5 daysNursing acceptability using questionnaire scores and thematic analysis of interviews30-day readmission rate

### Sample size and expected accrual

As the trial is designed to assess the feasibility of conducting a future definitive large-scale trial, a formal power calculation is not considered appropriate as effectiveness is not being formally evaluated.

According to the findings of Teare et al. [11], at least 120 subjects (60 in each group) will be required in the feasibility RCT to estimate event rates in the intervention arm with adequate precision. Anticipating an estimated consent rate of 30–50%, between 240 and 400 patients will be approached in order to recruit 120 participants.

In addition, it is possible that not all participants will be assigned a bed in a participating ward. Allowing for 20% of patients going to non-participating wards, with the expectation that this is likely to be balanced between the study groups, this necessitates that 300 to 500 patients will need to be approached and approximately 150 participants randomised in order to have monitoring data on 120 participants in total. With a 12-month recruitment period, this equates to 6–10 patients being approached on average per week.

Patients who are not admitted to a participating ward will be classed as ‘drop-out’ due to design and will not be included in the modified intention-to-treat analysis.

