### Randomisation

Following confirmation of eligibility and written informed consent, participants will be randomised into the trial by an authorised member of staff at the research site. Randomisation will be performed centrally using the University of Leeds Clinical Trials Research Unit (CTRU) 24-h randomisation service, either via the telephone or the CTRU website.

Participants will be randomised on a 1:1 basis and will be allocated a unique trial number. Randomisation will be conducted using stratified block randomisation with variable block size with sex (male/female) and ASA grade (grades 1–4) as stratification factors.

The randomisation sequence will be provided by a statistician in the Leeds Clinical Trials Research Unit and computer generated using SAS 9.4 (SAS Institute Inc., USA, 2013). This sequence will be implemented and delivered by programmers through the Leeds CTRU Gen24 system, a dedicated telephone and web-based randomisation service.

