### Interventions

Patients randomised to the ‘intervention’ arm will receive a patch and standard NEWS monitoring.

When the patient comes out of theatre, they are nursed in Recovery for a short time before being admitted on to the receiving ward. The patients allocated to receive the remote monitoring will, where possible, have the patch applied in Recovery by a member of the research team. If for any reason the patch cannot be applied in Recovery, it will be applied as soon as possible upon the patient’s return to one of the participating wards. If a participant is admitted to level II/III care after surgery and before returning to a participating ward, they will have the patch applied in Recovery but the patch will only be activated once the patient returns to the participating ward. This will usually be 1–2 days later.

Two colorectal surgery wards will be participating in the study: male and female. The male ward houses 25 beds, whilst the female ward houses 28 beds.

The patch will activate on arrival on the ward, and the patient’s nurse will carry a mobile device to alert them if the vital signs stray outside of normal parameters. Remote monitoring data will also be accessible on the ward computer screens for wider access. There will be no dedicated telemetry screen for the patch data.

Nursing staff will be provided with thorough training before the commencement of the study. This will involve training in the application and removal of the patch, the use of the mobile application and how to acknowledge alerts. If the mobile devices alert the nursing staff to abnormal vital signs, the ensuing clinical response is not mandated, but left to the nurse’s discretion.

In order to monitor alarm burden, the Clinical Fellow assigned to the trial will make daily ward visits and ask the nursing staff about false alerts. The Fellow will then adjust the monitor’s delays and thresholds on an individual basis and according to clinical need, for instance, adjusting the heart rate alert threshold in patients with pre-existing cardiac arrhythmias.

During these daily ward visits, the Fellow and the research nurse will also be responsible for changing expired patches and removing patches upon patient discharge. In order to optimise patient comfort and compliance with the device, it will also be possible to adjust or replace electrodes, including after patient washing.

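### The only named analysis population drops about a fifth of randomised patients on ward destination, an event after randomisation; patch-arm adherence is overstated if this is also its denominator

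*Protocol article*

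**What the plan says.** **Timing.** Under Recruitment, patients are approached and consented in the surgical admissions lounge on the morning of their operation; return to a study ward is only anticipated at that point. Under Randomisation: "Following confirmation of eligibility and written informed consent, participants will be randomised into the trial". Under Interventions, patients already allocated to the patch have it applied in Recovery where possible. For those who go first to level II/III care, "the patch will only be activated once the patient returns to the participating ward".

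**Planned loss.** Sample size and expected accrual sets the target: "at least 120 subjects (60 in each group) will be required in the feasibility RCT". It then adds: "Allowing for 20% of patients going to non-participating wards", "with the expectation that this is likely to be balanced between the study groups". This leads to "approximately 150 participants randomised in order to have monitoring data on 120 participants in total".

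**Population.** The same section says that patients who do not reach a study ward are dropped "due to design and will not be included in the modified intention-to-treat analysis". Planned analyses describes the mITT as everyone randomised, in their allocated group and whether or not they adhered, and then removes this group. It names no other population.

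**Outcomes affected.** Primary outcome measures include the number of patients who do not get the monitoring they were randomised to, and parameters for the definitive trial's sample size. Secondary outcome measures include critical care admissions, critical care stay and complications.

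**The concern.** Ward destination is decided after randomisation. It can depend on how the operation went, whether critical care was needed and for how long, and which beds were free. Removing patients on that basis has two consequences for a feasibility trial.

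1. **Delivery.** A patch-arm patient who never reaches a study ward has not received the allocated monitoring, because the patch is not activated elsewhere. This is a foreseen way for delivery to fail, and the plan sizes it at one patient in five. If adherence is reported on the mITT, this failure leaves both numerator and denominator, and the definitive trial would be planned on too favourable a figure.

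2. **Event rates.** A patient who dies in critical care, or does not step down from it to a study ward, is excluded, although critical care use and complications are among the outcomes to be estimated. Even if exclusions are balanced between arms, the mITT rates describe patients who reached a study ward. A definitive trial that randomises at the same time point would need rates for everyone randomised.

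**Working it through.** **Inputs from the protocol article.** 120 patients with monitoring data, 60 per group; 20% allowance for other wards; about 150 randomised; 1:1 allocation, so 75 per arm; consent rate 30–50%; complication rates of 33–44% cited in the Background.

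**The plan's own figures.** 120/(1 - 0.20) = 150, as stated. Approached: 150/0.5 = 300 and 150/0.3 = 500, as stated. Per week over 52 weeks: 300/52 = 5.8 and 500/52 = 9.6, stated as 6–10. The arithmetic is sound. The planned exclusion is 150 - 120 = 30, or 15 per arm if balanced.

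**When randomisation happens.** No sentence places it before surgery outright. It follows consent, consent is taken in the admissions lounge, and allocation is known by Recovery. Taken together, these put allocation ahead of the final ward.

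**Adherence in the patch arm.** Let d be the share excluded and a the adherence within the mITT. No excluded patch patient can have received active monitoring, so adherence among all randomised is a × (1 - d), and the mITT overstates it by 1/(1 - d). At d = 0.20 the factor is 1.25 and the ceiling is 60/75 = 80%. The values of a below are assumed, because the article gives none:

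| mITT adherence (of 60) | All randomised (of 75) |
|---|---|
| 100% (60) | 80% |
| 95% (57) | 76% |
| 90% (54) | 72% |
| 80% (48) | 64% |

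The 20% is an allowance, not a known share. With a held at 90%, d = 10%, 20% and 30% give 81%, 72% and 63%.

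Controls on other wards presumably still receive NEWS, which is their allocated monitoring, so the effect falls on the patch arm. Pooling the arms dilutes it: at a = 90%, (54 + 60)/120 = 95% becomes (54 + 75)/150 = 86%.

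**Event rates with balanced exclusion.** Let p be the rate in all randomised and q the rate in those excluded. The mITT rate is (p - d × q)/(1 - d), so it falls short of p by d × (q - p)/(1 - d). At d = 0.20 that is a quarter of the gap between q and p. As illustration, take p = 38.5%, the midpoint of the cited range, with q assumed:

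- q = 44%: (0.385 - 0.088)/0.80 = 37.1%, or 1.4 points low.
- q = 60%: (0.385 - 0.120)/0.80 = 33.1%, or 5.4 points low.

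If the excluded patients were at lower risk, the sign would reverse. The article gives no value for q.

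**Balance.** With 75 per arm, 20% exclusion in each and independent destinations, the difference in exclusion share has SD sqrt(2 × 0.2 × 0.8/75) = 6.5 points, giving a 95% range of about ±12.8 points by chance alone. Noticeable imbalance is therefore possible without any bias, which is why exclusions need to be shown by arm.

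**The case against.** The strongest case against has five parts.

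- **There is no contrast to bias.** The article says that "a formal power calculation is not considered appropriate as effectiveness is not being formally evaluated", and Planned analyses rules out a formal comparison of the arms. This stands. A reader might infer that the mITT comparison is biased. The documents do not support that: the patch is inactive until ward arrival, so the intervention cannot steer the first ward destination, and balanced exclusion produces no spurious difference. Bed allocation influenced by unblinded staff is conceivable, but nothing in the article describes it.
- **The adherence denominator is not stated.** The outcome is defined as a count with reasons, non-compliance is to be recorded, and denominators for single outcomes are commonly left to the statistical analysis plan, which exists but is not shown. A reader might infer that adherence will certainly be overstated. That goes too far; it follows only if the mITT is the denominator, which is how Planned analyses reads in general.
- **The progression rule is partly protected.** It counts patients who receive monitoring on the trial, so failure to reach a study ward already counts against the recruitment target. This stands, but it does not correct the delivery or event-rate figures.
- **The loss may have little to do with severity.** The article attributes the 20% to bed assignment and describes critical care stays before the ward as usually 1–2 days. The number excluded through critical care is unknown and may be small.
- **The exclusion is declared in advance and labelled modified.** True. Nothing is concealed, but no all-randomised summary is named beside it.

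**Conclusion.** The point holds as a should-fix. The protocol article fixes an exclusion based on an event after randomisation, sized at about 30 of 150, and names no all-randomised population. Balance is an expectation, and exclusion can be related to critical care and complication outcomes.

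The firm part of its size is the ceiling: at the planned allowance, no more than 60 of 75 patch-arm patients (80%) can receive the allocated monitoring, while the mITT could show 100%, a factor of 1.25. This rests on three conditions: randomisation precedes knowledge of the ward (inferred), the 20% applies to the patch arm, and the mITT is the adherence denominator. The effect on event rates has no firm size, because the article says nothing about risk in the excluded patients.

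The documents do not show a biased contrast between arms, and they do not make a change to randomisation timing necessary in a trial that is already recruiting.

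**What to change.** Amend Sample size and expected accrual and Planned analyses, and carry the change into the statistical analysis plan if it is not already there:

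1. Collect the record-based outcomes (critical care use, stay, complications, reinterventions, readmission) for everyone randomised, including those who never reach a study ward.
2. Report full intention-to-treat summaries on all randomised beside the mITT summaries.
3. Report the number excluded from the mITT by arm and reason, separating bed allocation from death in, or failure to step down from, critical care.
4. Show patch-arm adherence on both denominators: all randomised, and those who reached a study ward. The first describes delivery as a whole, the second adherence once the patch could be activated.

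The cost is record extraction for about 30 more patients. The outcome data come from routine clinical records, so patients face no extra procedures.

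Randomising only once a study-ward bed is confirmed would remove the problem at source. It is an option to weigh for the definitive trial. In this open trial it would mix patients randomised at two different time points and would require staff to randomise at unpredictable times, so it is not asked for here.

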### Planned analyses

Analyses have been pre-specified in a statistical analysis plan. The analysis of the primary and secondary outcome measures will take place when all participants have been followed up (i.e. 30 days after the last recruited participant’s date of discharge). No interim analyses are planned but safety data will be presented to the Multidisciplinary Advisory Group at regular intervals.

Analysis will be carried out following the principles of modified intention-to-treat (ITT). The modified ITT (mITT) population will include all participants randomised to the trial, analysed according to the treatment group to which they were randomised, regardless of adherence to the protocol. The mITT population will not include any participants who are classed as ‘drop-out’ due to design (i.e. those who were never admitted to a participating ward).

As this is a feasibility study, no formal comparison between the study arms will be undertaken. Summaries will be produced by subgroup to determine any differences between low- and high-risk patients. High-risk patients will be defined as ASA > 2 undergoing major + surgery or ASA = > 2 with a perioperative critical care admission.

Baseline characteristics will be summarised descriptively overall and by trial arm. No statistical comparison between trial arms will be made.

Quantitative secondary outcome measures will be summarised descriptively using appropriate summary statistics both overall and by trial arm (mean, standard deviation, range and median for continuous outcomes and frequency and percentages for categorical measures). Proportions of missing data will also be presented. Data from patients discharged before the 5 days has elapsed will be censored. Qualitative secondary outcomes including patient acceptability and nurse acceptability will be analysed using a thematic analysis approach.

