## Background

Patients having major surgery are at high risk of complications, some of which can be life-threatening. Rates of complications have been found to be as high as 33–44% in patients undergoing surgery for gastrointestinal cancers [1]. Patients who develop postoperative complications become progressively unwell, often over a short period of time. Early recognition of postoperative complications is crucial in reducing morbidity and preventing long term-disability; for patients with septic shock, there is an 8% increase in mortality for every hour of delay in antibiotic administration [2].

The more unwell a patient becomes, the more likely they are to require higher level care, on either high-dependency units (HDU; level II) or intensive care units (ICU; level III). Escalation of care comes at significant cost to both the patient and the health service and is associated with worse patient outcomes. The average cost of a level I (general ward) bed is £433/day, as compared to £1033/day for a HDU bed, and £1351/day for an intensive care bed [3]. Early detection and treatment of complications minimises the need for level II/III care, improves patient outcomes and produces significant cost savings.

One of the ways patients are monitored for complications is by recording on a chart their vital signs. The vital signs are used to form a score, the National Early Warning Score (NEWS), which can alert if the patient becomes unwell. The vital signs included in the NEWS score are blood pressure, heart rate, breathing rate, oxygen saturation, level of consciousness and temperature [4]. The NEWS score also takes into account the need for supplementary oxygen to maintain a patient’s saturations. Typically, in the postoperative period, NEWS will be calculated half hourly for the first few hours, and if the patient remains stable, the frequency will decrease to 2-hourly and then 4-hourly, until the patient is ready for discharge when the NEWS may be recorded only twice a day.

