Although NEWS has proven benefit, it suffers from several drawbacks. A 2012 study evaluated early warning scores in patients 48 h before an adverse event [5]. Of patients, 81% had a score indicative of deterioration, but recordings were ‘mostly incomplete’ with respiratory rate documented in ‘only 30% to 66%’. NEWS relies on manual observations, is time-consuming, and open to user interpretation. Vital signs are taken at predetermined intervals (typically 4-hourly), with patient deterioration possible between recordings. It has been suggested that the gap between observations is one of the primary failings of the NEWS system [6].

A solution to the problem of inadequate monitoring frequency is continuous monitoring at the bedside. Continuous monitoring is used in level II/III care, but is limited by “hard-wired” equipment, which tethers the patient to the bed space. This hinders patient mobility and potentially slows their recovery. One study tested ICU-style monitoring on a general ward and found that only 16% of patients remained connected in a 72-h period [7].

A number of systems have been designed that combine the benefits of a wearable, wireless patch with continuous monitoring of vital signs. One such device is the SensiumVitals® which monitors heart rate, respiratory rate and temperature continuously. The data are transmitted wirelessly every 2 min to a mobile device carried by the nurse which alerts when there is deviation from pre-set physiological norms.

It is hypothesised that the remote continuous monitoring system, as an adjunct to standard NEWS monitoring, will allow earlier detection of postoperative complications. This should reduce morbidity, which in turn should result in a decreased need for high dependency/intensive care.

Studies evaluating continuous monitoring of multiple vital signs parameters have shown mixed results. There is a preponderance of observational studies, which means that causal associations between interventions and patient outcomes have to be interpreted with care. An industry-funded controlled before-and-after study of 7643 patients [8] found that continuous monitoring on a medical-surgical unit was associated with a decrease in total ICU days, but the rate of ICU admission was unchanged.

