### Recruitment

Patients will be selected on the basis that they are undergoing elective major abdominal surgery and are anticipated to return to one of the participating wards afterwards. Types of surgery can include, but are not limited to, colorectal, upper gastrointestinal, liver, pancreas and biliary surgeries.

Table 1 illustrates the participant timeline for this study. Patients will be identified, recruited and consented for inclusion in the trial on the day of their surgery. This will take place on the General Surgical Admissions Lounge where patients attend on the morning of their elective procedures.

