**Table 1 Tab1:**
[figure not shown]
Schedule of enrolment, interventions, and assessments

The patients will be given information in the form of a patient information sheet regarding the study. Following a period of consideration, if they consent to participate in the study, they will be randomised into one of two monitoring arms.

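### One of the two routes into the high-risk subgroup is a post-randomisation critical care admission that is also counted as an outcome, so the subgroup HDU/ICU summaries are partly built in

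*Protocol article*

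**What the plan says.** Planned analyses in the protocol article gives the rule: "High-risk patients will be defined as ASA > 2 undergoing major + surgery or ASA = > 2 with a perioperative critical care admission". I read the second ASA condition as 2 or more. The purpose is stated just before it: "Summaries will be produced by subgroup to determine any differences between low- and high-risk patients". The same paragraph rules out testing: "As this is a feasibility study, no formal comparison between the study arms will be undertaken".

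On timing, Recruitment says "Patients will be identified, recruited and consented for inclusion in the trial on the day of their surgery", and the text under Table 1 adds that "if they consent to participate in the study, they will be randomised into one of two monitoring arms". Interventions has the patch applied in Recovery where possible, so allocation is known before any postoperative critical care stay.

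On outcomes, the Background identifies higher-level care as "high-dependency units (HDU; level II) or intensive care units (ICU; level III"). Secondary outcome measures lists the number of HDU/ICU admissions and the length of stay in HDU/ICU. Neither excludes a stay that begins straight after theatre. The Background hypothesis is that earlier detection should reduce morbidity, "which in turn should result in a decreased need for high dependency/intensive care".

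Two kinds of critical care stay appear. Interventions describes level II/III care between theatre and the ward, during which the patch is not activated. Data collection describes a later move from the ward to a critical care bed, during which monitoring is suspended. The second route is worded "with a perioperative critical care admission", and the rule does not say which of these 'perioperative' covers.

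**The concern.** A risk subgroup should be fixed by what is known before allocation. Here one route uses an event that follows allocation and is also tabulated as an outcome. When HDU/ICU admissions and HDU/ICU stay are summarised by risk group, part of the contrast comes from how the groups were formed and says nothing about underlying risk.

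Two things are at stake. First, Primary outcome measures includes estimating parameters for the sample size of a definitive trial and choosing its outcome measures. The Background also says that convincing evidence needs high-risk populations and outcomes such as critical care admission. An HDU/ICU rate from this high-risk group would be a natural planning value, and it would be inflated. Second, if the qualifying admission can occur after monitoring has begun, the intervention could change who is labelled high-risk, and the arms within a subgroup would no longer be the groups that were randomised.

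**Working it through.** **No stated figure to reproduce.** The article gives no subgroup size, ASA mix, share of major+ surgery or admission rate. The one planning figure used below is 60 per arm (Sample size and expected accrual).

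**Structural check (no assumptions).**
- Route A is ASA > 2 with major+ surgery. Route B is ASA ≥ 2 with a perioperative critical care admission.
- An ASA 2 patient fails route A, so can be high-risk only through route B. Every high-risk ASA 2 patient therefore has an HDU/ICU admission.
- If low-risk means everyone else, a perioperative admission in the low-risk group can come only from an ASA 1 patient.

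**Illustration (all inputs assumed).** Let ASA 1/2/3+ be 20/50/30%, let 60% have major+ surgery at every ASA grade, and let the perioperative admission rate be c = 20% for everyone. There is then no true difference to find, and any grouping by baseline data would show 20% in both groups.
- Route A share: A = 0.30 × 0.60 = 0.18.
- Share entering by route B only: B = (0.50 + 0.30 × 0.40) × 0.20 = 0.62 × 0.20 = 0.124.
- High-risk share: A + B = 0.304.
- Admitted among high-risk: (A × c + B)/(A + B) = (0.036 + 0.124)/0.304 = 0.526, about 53%.
- Admitted among low-risk: (0.20 × c)/(1 − 0.304) = 0.04/0.696 = 0.057, about 6%.

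**Range.** With c from 10% to 30%, major+ surgery from 30% to 90%, and ASA mixes of 10/60/30, 20/50/30 and 10/50/40%, the high-risk rate runs from 22% to 81% and the low-risk rate from 1% to 11%.

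**What the reading of 'perioperative' changes.** The percentages above concern the qualifying admissions.
- *Narrow reading (direct from theatre only).* Later ward-to-critical-care moves add to both groups, so low-risk ASA 2 patients can have an HDU/ICU admission. The qualifying stay is still counted in the outcomes, so the built-in contrast remains. The patch is inactive during that stay, so monitoring cannot alter membership.
- *Wide reading (ward moves included).* Membership can depend on arm. Keep the inputs above and suppose the intervention changes c:

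| c | Expected high-risk of 60 |
|---|---|
| 20% (control) | 60 × (0.18 + 0.62 × 0.20) = 18.2 |
| 15% | 60 × (0.18 + 0.62 × 0.15) = 16.4 |
| 10% | 60 × (0.18 + 0.62 × 0.10) = 14.5 |

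On this reading, by-arm summaries within a subgroup are conditioned on a post-randomisation event for every outcome, not only the HDU/ICU ones.

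**The case against.** The strongest reply is that 'perioperative' most naturally means the stay between theatre and ward described under Interventions. That stay precedes activation of the patch, so the intervention cannot prevent it through alerts and the arms within each risk group stay comparable. This largely stands. What is left is a possible effect of unblinded allocation on where a patient is sent, and the fact that the article does not settle the reading. The SAP, which was not available for this review, may define the window.

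A second reply is that the summaries are descriptive, with no test or decision rule attached, and that the progression criteria concern only recruitment and missing data. That also stands, and it limits the severity. It does not remove the point, because a descriptive rate can still be misleading and the trial is meant to supply planning parameters.

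A reader might infer more than the article supports:
- *That the whole subgroup is defined by an outcome.* It is not: route A does not use critical care admission, and route B also requires ASA 2 or more.
- *That every subgroup summary is circular.* Strict circularity reaches only HDU/ICU admissions and HDU/ICU stay. For total stay, complications, reinterventions, time to antibiotics and readmission, the issue is conditioning on a post-randomisation event.
- *That an effective patch must move patients from high- to low-risk, leave low-risk ASA 2 patients with no HDU/ICU admissions, or make a benefit on hospital stay look like harm.* The first two need the wide reading. The third also needs a link between severity and stay that the article does not quantify.

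**Conclusion.** The point holds on either reading for the two HDU/ICU outcomes. The rule makes a counted outcome event a ticket into the high-risk group, so the high- versus low-risk contrast on those outcomes is partly produced by the definition. The 53% v 6% shows how large this can be when there is no true difference. It rests on an invented case mix and a uniform admission rate, and real admission rates may well rise with ASA grade. Some of any observed contrast would then be genuine, but the planned tables could not separate it from the built-in part.

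Dependence of membership on arm is conditional: possible on the wide reading, not expected through monitoring on the narrow one. The documents do not support the conclusion that the randomised comparison as a whole, or the decision to progress, is compromised. Severity is moderate.

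**What to change.** Either of two changes would do.

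1. Define risk only from data fixed before randomisation: ASA grade, planned surgery grade and, if it is recorded, a planned critical care bed. Actual critical care admission is then reported only as an outcome. This is the cleaner option, and it yields a group that a later trial could identify at consent.
2. Keep the present rule, but limit 'perioperative' to a critical care stay before first arrival on a participating ward, and exclude that stay from the HDU/ICU admissions and HDU/ICU length of stay shown in the subgroup summaries. This removes the strict circularity and any shift through monitoring. The grouping would still rest on an event after allocation.

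The cost is about one sentence in the protocol or SAP. Under option 1, some patients with an unplanned critical care stay are no longer labelled high-risk. The article does not say whether a pre-operative bed booking is recorded, so that element is an assumption to confirm before relying on it.
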